### Statistical analysis

The objective of our study is to identify clusters based on predictive motivational variables related to PA and nutritional behaviors among older patients with cancer. The analyses to be conducted aim (i) to identify predictors of PA and nutritional behaviors and (ii) to identify groups of patients with similar patterns of relations between motivation and behavior.

We will evaluate the sample’s adherence to and acceptance of this original data collection with descriptive statistics such as the means, medians, and percentages. These measures will allow us to summarize the key characteristics of the dataset.

For the first step, we will use a Multilevel Vector-autoregressive model (mlVAR), as implemented in the R package “mlVAR.”. mlVAR model will be run in parallel for physical activity and nutrition separately. The mlVAR is a multilevel extension of the vector auto-regression (VAR) model, which describes dynamic relationships among variables measured repeatedly over time from multiple subjects [58]. This model has become a popular tool particularly in studies involving psychological variables [59]. In a contemporaneous network, mlVAR identifies relationships between variables over the same time interval. To observe the temporal dynamics between variables in mlVAR, lagged coefficients quantify the auto-regressive effect (one variable on itself) and cross-lagged effect (one variable on another variable). In this temporal network, these coefficients illustrate the predictive relationships between variables over time and identify potential causal relationships. As a hypothetical example, we can observe that intention at time *t* predicts behavior at time *t + 1*, suggesting a directional influence of intention on subsequent behavior over time.

In a second step, we will use clustering methods (e.g., k-means) based on the coefficients of the VAR model, to identify groups of participants with similar patterns of relationships between motivation and behavior (nutrition and PA). K-means analysis will be run in parallel for physical activity and nutrition separately. Silhouette coefficients will be used to evaluate the validity and stability of the clustering [60], by comparing how close a point is to its own cluster, which is equivalent of the similarities among all individuals in the same cluster, versus how far it is from the nearest neighboring cluster. Its values range from − 1 to 1, where 1 indicates good clustering and − 1 indicates inaccurate clustering. The Silhouette coefficients are particularly relevant, because no additional training data is required [61].

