### Patient selection

Recruitment is anticipated to be completed by April 2026, with the aim of enrolling 40 patients in total. The patients considered for inclusion are those who come for their oncogeriatric care at the Cancer Institute of Montpellier (ICM) which is referral centre in France. If patients are eligible, the study is proposed to them by the investigator. Patients have to meet the following inclusion criteria: being aged 70 or over, having cancer (solid tumors, all sites), having a Geriatric 8 (G8) score ≤ 14, being inactive, i.e., not meeting recommended PA levels of 150 min per week at moderate intensity, providing informed, written and expressed consent and having a social security affiliation.

The exclusion criteria are as follows: known presence of brain metastases, inability to participate in digital platform or physical tests, inability to eat orally, contraindication or inability to engage in PA, inability to follow up regularly for psychological, family, numerical, social or geographical reasons and lack of liberty or under protective custody or guardianship.

This research will be conducted in accordance with the French Public Health Code, the Good Clinical Practice and the Declaration of Helsinki. This study has been registered on clinicaltrial.gov (NCT06445140). This research project has been approved by the national ethics committee (Comité des Personnes Nord Ouest III, accepted on 30 May 2024) and the “Agence nationale de sécurité du médicament et des produits de santé” (ANSM, French National Agency Authority for the Safety of Health Products) has been informed (19 June 2024). Written informed consent was obtained from all participants prior to inclusion in the study. Data will be securely stored using EasyMedStat software.

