#### Motivation toward physical activity and nutrition

Twice a day patients are asked about their motivation toward PA and nutrition over the next few hours: in the morning (between 8am to 10am) and at midday (between 12pm and 2pm). For each behavior, the questionnaire comprised five items corresponding to the TPB and assessing the following constructs: attitudes, both affective (e.g., “In my opinion, doing physical activity for at least 10 minutes in the next few hours would be a source of pleasure”) and instrumental (e.g., “For me, engaging in physical activity for at least 10 minutes in the next few hours would be beneficial for my health”); subjective norms, referring to perceived social approval from family members, significant others, or health professionals (e.g., “For me, doing physical activity for at least 10 minutes in the next few hours would be approved by most of the important people in my life”); perceived behavioral control (e.g., “It would be easy for me to do physical activity for at least 10 minutes in the next few hours”); and intention (e.g., “I intend to engage in physical activity for at least 10 minutes in the next few hours”). Each item uses a 7-point numeric scale to estimate motivation toward the behavior, with threshold values: 1 Not at all – 3 A bit – 5 Quite – 7 Very much. These questions were created following the guide to prepare a TPB questionnaire [50]. To validate these questionnaires, 7 patients with similar profiles to those likely to be included were asked about their understanding of the questions. To avoid repetitions during the study, 5 different versions were created and alternatively presented (see the complete list in the supplementary files).

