## Discussion

### Expects findings

This study aims to identify clusters based on predictive motivational variables related to PA and nutritional behaviors among older patients with cancer, via repeated measures. First, sufficient patient participation and adherence to the protocol are expected, with a good compliance completion rate for EMA and Actigraph GT3X-BT wear. Compliance was considered good if at least 70% of the planned EMA measures were completed across the study period, with fewer than 30% of missed responses. Participants were considered non-compliant if they responded to less than 50% of prompts. Participation and compliance will enhance our knowledge about how EMAs and accelerometers can be used among older adults during cancer treatment. With mlVAR analysis, we will attempt to identify predictors of behaviors based on motivational variables. Second, the analyses should identify groups of patients with similar patterns of relationships between motivation and behavior, by using clustering methods (e.g. k-means) based on the coefficients of the mlVAR model.

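### The silhouette coefficient is given the job of showing both validity and stability of the clusters, but it cannot represent a single group and does not measure stability

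*Protocol article*

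**What the plan says.** The section Statistical analysis of the protocol article describes a second step after the multilevel VAR model: "we will use clustering methods (e.g., k-means) based on the coefficients of the VAR model". It is done twice: "K-means analysis will be run in parallel for physical activity and nutrition separately". The quality of the result is then assigned to one index: "Silhouette coefficients will be used to evaluate the validity and stability of the clustering". The article explains that the index sets closeness to the patient's own cluster "versus how far it is from the nearest neighboring cluster". Only the ends of the scale are interpreted, "where 1 indicates good clustering and" −1 the reverse.

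Patient selection gives the size of the study, "with the aim of enrolling 40 patients in total". Expects findings, in the Discussion, anticipates the outcome: "the analyses should identify groups of patients with similar patterns of relationships between motivation and behavior". Creation of an intervention says that new patients will be matched to these clusters so that the intervention can be tailored. Strengths and limitations names the silhouette again, as a preliminary test mentioned together with possible changes to recruitment. Nowhere does the article say what would be concluded if the patients formed one group.

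**The concern.** Two properties are attributed to an index that does not carry them as stated.

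- **Validity.** An index that needs a nearest other cluster has no value for one cluster. Comparing it across numbers of clusters can rank two, three or four groups, but never one group against several. K-means divides any data set into the number of groups requested, so the possibility that patients differ only gradually needs a separate check.
- **Stability.** Stability asks whether the same patients would be grouped together again in another sample. The silhouette describes compactness and separation in the sample at hand and repeats nothing.

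Finding groups is the stated objective, and the interventional part assigns new patients to them. If a division of one continuous population were taken for real types, tailored content would rest on it.

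**Working it through.** **No figure to reproduce.** The article states no silhouette value, cut-off or sample-size derivation.

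**Definition.** For patient i, let a be the mean distance to the other members of the patient's cluster and b the smallest mean distance to the members of any other cluster. Then s(i) = (b − a) / max(a, b), and the index is the mean of s(i). With one cluster, b does not exist. No term involves a second sample or a resample.

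**Inputs.** From the article: n = 40, k-means, and five motivational items per behavior ("the questionnaire comprised five items corresponding to the TPB"). Five items plus the behavior make 6 variables, or 7 if fatigue is entered. Assumed, because the article does not say which coefficients are clustered: 5 to 7 if only paths into the behavior are used, 7 × 7 = 49 for the full temporal matrix, and 2 as a small case. The correlations of 0, 0.5 and 0.8 are also assumed.

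**Simulation, one population.** 40 patients were drawn from a single multivariate normal distribution. K-means was run with k = 2 to 6 and the best mean silhouette kept (150 runs per setting; 100 for 5 correlated coefficients). Values are means or medians, which agree within about 0.01 where both exist. Stability is the mean adjusted Rand index (ARI) between the partition and its bootstrap versions (25 data sets, 15 resamples each). The 0.25 mark is an assumed level, not one in the article.

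| Coefficients | Correlation | Best silhouette | 5th–95th percentile | Runs above 0.25 | Bootstrap ARI |
|---|---|---|---|---|---|
| 49 | 0 | 0.04 | 0.03–0.05 | 0% | 0.06 |
| 7 | 0 | 0.16 | 0.14–0.19 | 0% | 0.31 |
| 5 | 0 | 0.20 | 0.18–0.23 | 1% | 0.36 |
| 49 | 0.5 | 0.26 | 0.20–0.33 | 60% | 0.69 |
| 7 | 0.5 | 0.30 | 0.24–0.37 | 93% | 0.76 |
| 5 | 0.5 | 0.32 | 0.26–0.39 | 98% | not run |
| 2 | 0 | 0.40 | 0.36–0.46 | 100% | 0.63 |
| 5 | 0.8 | 0.44 | not tabulated | not tabulated | not run |

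**Simulation, two true groups.** Two groups of 20 were separated by d SD on one of 7 independent coefficients (60 runs). The best silhouette was 0.18 (d = 2), 0.24 (d = 3), 0.33 (d = 4) and 0.47 (d = 6).

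**Reading.**

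1. The same value means different things in different settings. One population with 7 coefficients correlated at 0.5 gives 0.30, above the 0.24 from two true groups 3 SD apart on 7 independent coefficients. A fixed cut-off does not cure this: at 0.25 a single population passes in anything from 0% to 100% of runs.
2. Stability does not follow the silhouette across settings. One population with 2 coefficients gives silhouette 0.40 and ARI 0.63. Two true groups at d = 6 with 49 coefficients give silhouette 0.14 and ARI 0.94.
3. Stability alone does not prove groups either: one population with 7 correlated coefficients reaches ARI 0.76, against 0.72 for two true groups at d = 3. Both checks are needed.

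**Check of a one-population reference.** With 7 coefficients, the best silhouette (k = 2 to 4) was compared with 39 draws from one normal distribution fitted to the same patients, at the 5% level. More than one group was declared in 0 of 60 one-population runs (independent) and 3 of 60 (correlation 0.5). With two true groups (30 runs each) it was declared in 0% at d = 3, 27% at d = 4 and 100% at d = 6. The low figures are understandable: two equal groups d apart add d²/4 to the variance of that coefficient (1 + 9/4 = 3.25 at d = 3), and the fitted single normal absorbs this as spread.

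**The case against.** A reader might infer more: that the plan will report groups whatever the data, that it cannot fail to find them, or that a positive result carries no evidence. The article does not support this. It says the silhouette will evaluate the clustering. It does not say that the number of clusters is the one with the highest silhouette, or that the winner is accepted as real. A value near zero could be read as weak structure, and an analysis plan that is not shown may add a cut-off or a one-group outcome. The sentence in Expects findings is an expectation, not a decision rule. Within one fixed setting the index does discriminate: with 7 independent coefficients, 0.16 for one population against 0.33 and 0.47 for groups 4 and 6 SD apart.

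It is also fair that the large values arise only under correlation or in low dimension, that neither the coefficients to be clustered nor their correlation is in the article, and that the simulation clusters coefficients directly, without mlVAR estimation error or shrinkage. The article leaves the algorithm open, and Strengths and limitations concedes that patient numbers and series length may limit the analysis.

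These points limit the consequence and its size. They do not remove the core: the article itself attributes stability to an index that does not measure it, and the index cannot represent one group. Neither is a detail left for later.

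**Conclusion.** The point holds in a bounded form. The only criterion named in the article for validity and stability is undefined for a single group and contains no information on reproducibility. In homogeneous data with 40 patients its best value runs from about 0.04 to about 0.44, depending on the number and correlation of the coefficients. A moderate value, in the range 0.2 to 0.4, therefore cannot be read as evidence of real groups without a reference built for the data. The range rests on assumed dimensions and correlations, normal data, k from 2 to 6, and no modelling of mlVAR estimation. It shows how much the index depends on the setting; it does not predict what this study will find, or that groups will be reported wrongly.

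**What to change.** Three changes, for the physical activity and the nutrition clustering alike:

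1. Take stability out of the silhouette's role and assess it by bootstrap resampling of patients, reported as a Jaccard or adjusted Rand index.
2. Report the observed silhouette beside its distribution under a one-population reference, for example a parametric bootstrap from the fitted mlVAR model that repeats estimation and clustering, or a gap statistic.
3. State that no distinct groups, meaning continuous heterogeneity, is an allowed result, and say what the interventional part would then use.

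The cost is computation and wording, plus a real loss of sensitivity. In the check above, the reference comparison at n = 40 found two true groups in 0% of runs at 3 SD, 27% at 4 SD and 100% at 6 SD. It is better reported as context than used as a hard gate. Failure to exceed it should be described as no demonstrated clusters, not as proof that the patients form one population.

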### Creation of an intervention

The results of the observational part of MONAGE will support the design of an effective and optimized behavior-change intervention for elderly cancer patients, thanks to a tailored approach of the relations between motivation and behaviors. The goal of the interventional part of MONAGE will be to improve physical activity and nutritional behaviors in a new sample of participants. This intervention will be designed in collaboration with patients, their caregivers / partners, doctors, dieticians, adapted physical activity teachers (kinesiologists), and behavior change professionals. Intervention content will be targeted on the most relevant strategies, based on the results in the observational phase; in other words, the choice and use of behavior change technique [62, 63], which are known to significantly lead to a change of PA behavior [64] and nutrition [65]. For example, “13.2. Framing/reframing”, a behavior change technique which is known to significantly influence attitudes toward the behavior [66], will only be proposed to participants for whom attitudes toward the behavior attitudes have emerged as a significant predictor of the behavior. For this purpose, during the interventional phase of MONAGE, each patient will undergo a one-week data collection period, similar to that of the observational phase, to determine whether they belong to one of the clusters identified during the observational phase. This identification phase then allows for the delivery of the intervention tailored to the patient’s profile.

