### Outcomes measures

Data collection begins the day after inclusion and lasts for 14 days. The data are collected via digital scales on the UniQ application via an EMA approach and a GT3X accelerometer worn on the waist. To observe whether the protocol seemed feasible for patients during the creation of the intervention, 7 patients with similar profile to those likely to be included were questioned about the frequency and duration of data collection. The retained configuration (i.e., answering to 3 very short questionnaires per day, and wearing the accelerometer for 14 days) suited both the patients and the investigators. The estimated time taken to complete the 3 questionnaires for a patient is 10 min per day, i.e. 4 min for the morning and midday questionnaires (12 items) and 2 min for the evening questionnaire (2 items). Every time a questionnaire is sent, patients receive an automatic e-mail informing them that a questionnaire is available on their UniQ platform and inviting them to answer. If necessary, the patient is informed that the caregiver can help him to complete the questionnaires.

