#### Physical activity

The PA data are measured via an accelerometer (ActiGraph GT3X-BT), which provides a reliable and valid objective measure [51]. Patients are instructed to wear the device on their nondominant waist all day for the entire data collection period, except during the sleep period. The ActiGraph GT3X-BT accelerometer provides a device-based measure of PA. If patients engage in activities where the monitor could get wet (e.g., swimming, showering or bathing), they are instructed to remove it. The data are recorded in 30-second epochs. Two day-segments were defined: midnight to 1pm for morning PA and 1pm to midnight for afternoon PA.

The PA intensity is graded based on the Euclidean Norm Minus One (ENMO). The objective is to indicate the threshold intensity based on ENMO to separate inactivity from light, light from moderate, and moderate from vigorous PA, respectively. We will use the following cutoff points: 14 for light (threshold.lig) and 70 for moderate (threshold.mod) intensity PA. These cutoff points are based on two studies among older adults: Sanders et al., in a sample of participants aged from 60 to 86 years old, set the cutoff points at 15 for threshold.lig and 69 for threshold.mod [52], and Migueles et al., among participants older than 70 years old (mean equal to 78.7 years old) defined cutoff points as 18 for threshold.lig and 60 for threshold.mod [53].

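### New patients are to be placed in clusters from one week of data, and the only named stability check, the silhouette, cannot show that such a placement reproduces

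*Protocol article*

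**What the plan says.** The Statistical analysis section plans a multilevel VAR for each behaviour, followed by k-means "based on the coefficients of the VAR model, to identify groups of participants with similar patterns of relationships between motivation and behavior". The data behind the clusters cover two weeks: "Data collection begins the day after inclusion and lasts for 14 days". To judge whether the clusters are valid and stable, the section names silhouette coefficients and nothing else. Strengths and limitations names the silhouette again, as a preliminary test.

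Creation of an intervention then halves the window for new patients: "each patient will undergo a one-week data collection period, similar to that of the observational phase". The purpose is "to determine whether they belong to one of the clusters identified during the observational phase". Content follows from the result. For example, a technique aimed at attitudes goes only to participants for whom attitudes "have emerged as a significant predictor of the behavior". The text does not say how a new patient's week is turned into a cluster.

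Two other statements bear on this. Preprocessing data says that within-person dynamics need some minimum of observed data and leaves that minimum open. Strengths and limitations concedes that series length may limit the analysis even at 14 days. Neither statement is carried over to the one-week window.

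**The concern.** The clusters are meant to be used through a one-week measurement, but nothing planned would show that one week is enough. A silhouette compares each patient's distance to their own cluster with the distance to the nearest other cluster, within a single fit. It takes each patient's coefficients as given. Noise in those coefficients, and whether a second week would give the same ones, lie outside what it measures. A high silhouette is therefore compatible with assignments that change from week to week.

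The stake is practical. The study could report well-separated clusters that cannot be recognised in a new patient from seven days, and the tailoring would then partly follow noise. The 14-day data contain two separate weeks per patient, so the question can be examined before the one-week window is relied on.

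**Working it through.** The protocol gives no figure in support of the one-week window, so there is none to reproduce. The counts below follow from its schedule.

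**Inputs**
- Motivation occasions: "Twice a day patients are asked about their motivation toward PA and nutrition over the next few hours", so 2 per day.
- Motivation variables: for each behaviour "the questionnaire comprised five items corresponding to the TPB", so 5.
- Physical activity: "Two day-segments were defined: midnight to 1pm for morning PA and 1pm to midnight for afternoon PA", so 2 values per day. Intake is also asked twice a day (Nutrition).
- Fatigue: measured three times a day; whether it enters the model is not stated.
- Compliance: about 80% reported for older adults (Introduction); 70% or more counted as good (Expects findings).
- Target enrolment: 40 (Patient selection).

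**Parameters per equation.** Five motivation items plus the behaviour give 6 slopes and an intercept: 7. With fatigue: 8.

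**Lag-1 steps.** One week has 7 × 2 = 14 occasions, so 14 − 1 = 13 steps if nights are kept, or 7 if only within-day steps count. Two weeks give 27 or 14. If missed prompts are independent and both ends of a step are needed, usable steps = steps × compliance².

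| Window | Lags | Complete | 80% | 70% |
|---|---|---|---|---|
| 7 days | nights kept | 13 | 8.3 | 6.4 |
| 7 days | within-day | 7 | 4.5 | 3.4 |
| 14 days | nights kept | 27 | 17.3 | 13.2 |
| 14 days | within-day | 14 | 9.0 | 6.9 |

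With complete data and nights kept, one week leaves 13 − 7 = 6 or 13 − 8 = 5 residual degrees of freedom. This treats a gap of about 4 hours (8–10am to 12–2pm) and one of about 20 hours as the same lag. Within-day, 7 − 7 = 0 remain, or there are fewer steps than parameters. At 70% compliance both one-week counts fall below 7.

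One allowance favours the plan. The accelerometer does not depend on prompts, so the physical activity equation taken alone needs only the earlier prompt. That gives 13 × 0.7 = 9.1 or 7 × 0.7 = 4.9 steps at 70%, which leaves 1 to 2 degrees of freedom with nights kept and none within-day. Kalman imputation restores the nominal count but adds no information.

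**Illustrative simulation with two true clusters.** Assumptions, none from the protocol: clusters differ in which motivation item drives behaviour; standardised lag effect 0.3 or 0.5; 6 variables; 40 patients with 14 days; k-means on the behaviour-equation coefficients; new patients assigned to the nearest centre; 40 replicates per setting; compliance 100%, 80% and 70%.
- Stand-alone least squares, one week: with nights kept, not estimable in 22–23% of patients at 80% compliance and 52–53% at 70%; within-day, 96–99%.
- Shrinkage estimate given the true prior, which favours the plan: correct one-week assignment 54–78% (nights kept) or 52–70% (within-day). Week 1 and week 2 agree in 59–68% or 58–63%.

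The nominal chance value for two equal clusters is 50%, but part of the agreement is not recognition. If each week were right with probability p, independently and equally in both clusters, agreement would be p² + (1 − p)². At p = 0.541 this is 0.293 + 0.211 = 0.503, whereas that setting gave 0.593. The excess suggests unequal fitted clusters, so the true no-signal value probably lies above 50%.

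**Why the reference must be simulated.** Take three groups, with centres fitted on both weeks and a per-week slope standard error of 1/√5 = 0.447. With no real differences between patients, the two weeks still agree in 49% (kappa 0.23), because both helped to build the centres. With assigned patients held out, no signal gives about 36%, and between-patient slope SDs of 0.1 to 0.3 give 38–46%.

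**Precision of the check.** With 40 patients the 95% half-width is 1.96 × √(0.8 × 0.2/40) = 0.124 at 80% agreement and 1.96 × √(0.6 × 0.4/40) = 0.152 at 60%.

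**The case against.** The strongest reply is that the protocol never says a new patient gets a stand-alone VAR. It specifies a multilevel model that pools across patients, and assignment could borrow from it. That is right. A reader might infer from the step counts that one week cannot support any assignment, but the text does not carry this. The rule is undescribed, a pooled estimate is computable, and a single equation can be fitted with complete data and nights kept. What remains is that pooled assignment reproduced only modestly better than chance in the simulation, and nothing planned would reveal this.

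Three further inferences should not be drawn:
- **A significance test in each patient.** The wording on significant predictors could suggest this, but the same section says the week serves to determine cluster membership, so a cluster-level reading is equally open. Single-patient power and false-positive rates are therefore not a fair charge.
- **Irrelevant coefficients swamping the motivation-to-behaviour slopes.** The protocol does not say that every coefficient is clustered or that fatigue is included. Any gain from clustering only five slopes depends on the assumed gap and on the rest carrying no signal. Under the Theory of Planned Behavior, attitudes, norms and control also act through intention.
- **One in three as the chance level for three clusters.** The 49% above shows this is wrong when the same weeks build the centres.

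It is also fair that this article covers the observational part, whose stated aims are predictors and groups. The interventional part is only sketched and may get its own protocol. That limits the weight of the point. But the article already commits to one week, and the observational data are the natural place to test it.

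**Conclusion.** The point holds in a limited form. The protocol fixes a one-week assignment window for clusters built on two weeks, does not state the assignment rule, and offers as evidence of stability a measure that cannot show reproducibility. The step and parameter counts follow from the protocol's own schedule; the figures under missing data add the assumption of independent missed prompts. On those counts a stand-alone one-week estimate is barely estimable or not estimable. For pooled estimates the evidence is illustrative only: 58–68% week-to-week agreement against a nominal 50%, under assumed effects and a prior known exactly. It shows that reproducibility cannot be taken for granted. It does not show that one-week assignment must fail.

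**What to change.** - State the rule that turns a new patient's week into a cluster: which estimate, which coefficients, what prior or pooling, how overnight gaps are treated, and when no assignment is made.
- Add a split-week reproducibility analysis. In leave-out folds, fit the multilevel model and the clusters without the held-out patients. Assign each held-out patient from week 1, from week 2 and from all 14 days, imputing within each week so that one does not inform the other. Week 1 against week 2 is the main comparison, since the 14-day assignment shares data with both.
- Report agreement as kappa or adjusted Rand index with a confidence interval, beside a no-signal reference obtained by simulation or permutation through the same procedure.
- Treat one-week assignment as supported only if out-of-sample agreement clearly exceeds that reference, for example if the lower confidence limit lies above it.
- Keep the silhouette as a measure of cohesion and separation, and stop describing it as evidence of stability.
- Clustering on the motivation-to-behaviour slopes alone may be run as a sensitivity analysis.

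The cost is analysis time and wording, with no added visits or patients. The estimate will be imprecise with 40 patients, and the report should say so.
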